# 1 CONTEXT OF THE RAP DEVELOPMENT

This statistical analysis plan (SAP) describes the epidemiological approach used to investigate the progression from an initial cervical HPV infection to cervical pre-cancer and cancer. As most HPV infections are cleared by the immune system and do not result in clinical complications such as cervical pre-cancer and cancer, the clearance of HPV infections will be also investigated. In addition, the time to first HPV infection and to first persistent HPV infection will be explored.

Thus, the study objectives are to describe the following outcomes:

- i) the time between confirmed persistent cervical HPV infections and the development of CIN associated with the same HPV type,
- ii) the time between any cervical HPV infections and the development of CIN associated with the same HPV type,
- iii) the clearance of cervical HPV infections,
- iv) the time between the start of sexual activity and a first incident or a first persistent cervical HPV infection,

and to assess the effect on these outcomes of determinants such as sexual behavior, smoking history etc. known to predispose subjects to cervical HPV infections and/or clinical complications of HPV infections such as pre-cancer and cervical cancer.

The analyses will be performed using data obtained from the subjects included in the control arm of the HPV-008 study (End-of-Study (M48) database from the Phase III pivotal study to evaluate the efficacy of HPV-16/18 VLP AS04 vaccine compared with control HAV vaccine).

More specifically, analyses will include the use of the following data collected at enrolment and during all the visits over the 48-month follow-up of the control arm subjects included in the HPV-008 study:

- i) virological (cervical HPV infection detected by PCR in cervical liquid-based cytology (LBC) samples),
- ii) cyto-pathological examinations on LBC samples and histology samples (colposcopy performed according to the clinical management algorithms defined for the HPV-008 study),
- iii) HPV-16/18 serostatus (by ELISA) at enrolment,
- iv) socio-demographic and behavioral data.

Of note, the results of the analysis of the time between the start of sexual activity and a first incident or a first persistent cervical HPV infection will be presented in a stand-alone statistical report.

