### 3.2 Study procedures resulting in data to be used for analyses

- Blood samples for all subjects were drawn at Months 0, 7 and 24 and in a subset of subjects from selected study sites.
- Gynecological examinations were performed at Months 0, 12, 24, 36 and 48.
- Cervical liquid-based cytology samples were collected at Months 0, 6, 12, 18, 24, 30, 36 and 48:
  - HPV DNA typing by PCR was performed on cervical liquid-based cytology samples at Months 0, 6, 12, 18, 24, 30, 36 and 48,
  - Cytopathological examinations were performed on liquid-based cytology samples to detect abnormal cells at Months 0, 12, 24, 36 and 48 in all subjects,
  - Screening for *Chlamydia trachomatis* and *Neisseria gonorrhoeae* on liquid-based cytology samples at Months 0, 12, 24, 36 and 48.

Note: As of Protocol Amendment 2, screening for *Neisseria gonorrhoeae* was done only if considered appropriate by the investigator.

- Colposcopic referral according to appropriate clinical management algorithms. A central laboratory processed and interpreted results from liquid-based cytology and histology samples. All CIN endpoints were confirmed by an expert histopathology review panel that was blinded to vaccine status, HPV DNA status before biopsy and cytology reports. An Endpoint Committee was responsible for reviewing all available clinical and laboratory data prior to study unblinding by the external statistician to make final case assignments for all subjects assumed to meet criteria for primary and secondary efficacy endpoints.

- Behavioral questionnaire completed by interview for all subjects at Months 1, 12, 24, 36 and 48. The behavioral questionnaire (self-administered) collected specific socio-demographic and behavioral data concerning determinants that are recognized to predispose subjects to cervical HPV infection or are recognized co-factors for cervical carcinogenesis. The baseline questionnaire assessed at Month 1 collected data which occurred during past history and during the previous year. Questionnaires assessed at Month 12, 24, 36 and 48 collected data assessed during the previous year.

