  - *Definition 1:* the clearance of an cervical HPV infection, whether incident, transient or persistent, with a given HPV type is defined as the occurrence of at least **a negative sample** for HPV DNA (by PCR) of that HPV type at the evaluation performed 6 months after the evaluation when the incident or transient cervical HPV infection was detected or when the last positive sample of the 6-month or 12-month persistent cervical HPV infection was detected.
  - *Definition 2:* the clearance of an cervical HPV infection, whether incident, transient or persistent, with a given HPV type is defined as the occurrence of at least **two negative samples** for HPV DNA (by PCR) of that HPV type at the evaluation performed 6 month after the evaluation when the incident or transient cervical HPV infection was detected or when the last positive sample of the 6-month or 12-month persistent cervical HPV infection was detected.

The flowchart in Section 8.2 provides an example of the determination of cervical HPV infection endpoints for a given HPV type.

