#### 4.3.2 Histopathological CIN associated with HPV type

The section 4.4.2.1 of the RAP for the HPV-008 efficacy study (dated 8 August 2009) provides an overview of the histopathological endpoint determination process and the section 4.4.4.2 of the RAP details the case definition of histopathological endpoints.

A **histopathologically confirmed CIN** can be detected in the biopsy sample after colposcopy or in the excision specimen after treatment.

Histopathologically confirmed CIN include:

- **CIN1+:** Cervical intraepithelial neoplasia as CIN1, CIN2, CIN3, adenocarcinoma in-situ and invasive cervical cancer,
- **CIN2+:** Cervical intraepithelial neoplasia as CIN2, CIN3 adenocarcinoma in-situ and invasive cervical cancer.
- **CIN3+:** Cervical intraepithelial neoplasia as CIN3 adenocarcinoma in-situ and invasive cervical cancer.

The **histopathologically confirmed CIN associated with a given HPV type infection** will be defined at a subject level. A subject might have multiple lesions associated with different HPV types at the same time point or at different time points.

As for the HPV-008 efficacy study, the current study will include only histopathological endpoints which were confirmed by the study Endpoint Committee.

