#### **6.2.4.4 Time computation**

The time between the onset of a confirmed persistent cervical HPV infection (6-month definition) and a histopathologically-confirmed CIN2+ (or CIN1+, or CIN3+) associated with the same HPV type will be calculated in days as: Date of event or Date of censoring - Date of detection of the 6-month HPV persistent infection.

The date of event will be:

- the date of the detection of the histopathologically-confirmed CIN2+ (or CIN1+, or CIN3+) associated with the same HPV type as the HPV type of the 6-month persistent cervical HPV infection,

The date of censoring will be:

- the date of Month 48 visit for subjects who attended all visits during the 48-month follow-up period and who had a histopathologically-confirmed CIN2+ (or CIN1+, or CIN3+) not associated with the same HPV type as the 6-month persistent cervical HPV infection or who did not have a histopathologically-confirmed CIN2+ (or CIN1+, or CIN3+) or during this period,
- the date of the last PCR reported at the latest visit for which data are available or the date of the last cytology or the date of the last biopsy (if the date is after the date of the last PCR) for subjects who did not attend all visits during the 48-month follow-up period and who had a histopathologically-confirmed CIN2+ (or CIN1+, or CIN3+) not associated with the same HPV type as the 6-month persistent cervical HPV infection or who did not have a histopathologically-confirmed CIN2+ (or CIN1+, or CIN3+) throughout their follow-up period (from first to last visit).
- Special cases:
  - In case two distinct 6-month persistent cervical HPV infections (i.e. separated by a clearance) associated with the same HPV type are detected for a same subject and a histopathologically-confirmed CIN2+ (or CIN1+, or CIN3+) associated with this HPV type is detected after the second infection, the date of censoring of the first infection will be the date of onset of the second infection since the event (i.e. detection of a histopathologically-confirmed CIN2+ (or CIN1+, or CIN3+)) is associated with the second detected infection (in chronological order).

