### 9.3.3 Analysis of clearance of cervical HPV infections

One flowchart will be presented for each the two definitions of clearance of HPV cervical infections.

[figure not shown]

All infections are taken into account.

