| #2 |         | HPV16   |          |          |              |          |              |          | n        | NA    |               | 
 
Subject #2 had a transient HPV16 cervical infection detected at month 6 but no 6-month persistent cervical HPV infection throughout the 48-month follow-up period.
 
No persistent cervical HPV infection is included in the analysis (subject not included in the analysis).
 
                                                                                                                          |
| #3 |         |         | HPV 16   | HVP16    |              |          |              |          | y        | n     | 36 (censored) | 
 
Subject #3 had a 6-month persistent HPV16 cervical infection detected at month 12 and no CIN detected throughout the 48-month follow-up period.
 
One persistent cervical HPV infection is included in the analysis with a censored time-to-event value of 36 months and HPV type = 16.
 
                                                                                                                |
| #4 |         |         |          | HPV18    | HPV18        |          | CIN3 (HPV33) |          | y        | n     | 24 (censored) | 
 
Subject #4 had a persistent HPV18 cervical infection detected at month 24 and a CIN3 associated with HPV33 at month 42.
 
One persistent cervical HPV infection is included in the analysis with a censored time-to-event value of 24 months and HPV type = 18 (note: time-to-event value is censored because CIN3 is not associated with the same HPV type as the persistent cervical HPV infection).
 
 |

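### Excisional treatment is ignored: HPV negativity after excision is coded as clearance, and time after treatment stays at risk in the lesion analyses

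*SAP*

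**What the plan says.** **Aim.** SAP section 1 motivates the clearance analysis biologically: "As most HPV infections are cleared by the immune system and do not result in clinical complications".

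**Treatment occurs.** Section 3.2 lists "Colposcopic referral according to appropriate clinical management algorithms", and section 4.3.2 says that a confirmed CIN "can be detected in the biopsy sample after colposcopy or in the excision specimen after treatment".

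**Clearance.** Under both definitions in 4.3.1, "the clearance of an cervical HPV infection, whether incident, transient or persistent, with a given HPV type is defined as the occurrence of" negative samples, one or two, "for HPV DNA (by PCR) of that HPV type at the evaluation performed 6 months after the evaluation when the incident or transient" infection was found (for persistent infections, after the last positive sample). Section 6.2.6.3 codes the result 0 or 1. The flowchart note in 9.3.3 adds: "All infections are taken into account". The covariates in 9.5.2 are HPV type, region, behavioral items, previous infection and co-infection. There is no lesion or treatment term.

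**Time to lesion.** Censoring in 6.2.4.4 is "the date of Month 48 visit for subjects who attended all visits during the 48-month follow-up period and who had a histopathologically-confirmed CIN2" or worse of a different type, or who had no such lesion. For women who missed visits it is the last PCR, cytology or biopsy. Section 6.2.5.4 repeats this for any infection. Treatment is not a censoring event. In 9.4.1, subject #4 has HPV-18 from Month 24 and an HPV-33 CIN3 at Month 42: "One persistent cervical HPV infection is included in the analysis with a censored time-to-event value of 24 months and HPV type = 18". The lesion models (4.4.2, 9.5.1) do carry a time-dependent covariate for an intervening CIN of a different type.

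**The concern.** Excision can remove the infected tissue. A negative PCR afterwards then reflects the procedure rather than the immune response that section 1 sets out to study. Such infections were still present when the woman was treated, yet they enter the model as successes. HPV type is the main variable of interest in 9.5.2, so if types differ in how often they lead to treatment, the type contrast is distorted and no covariate can absorb it.

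In the lesion analyses, a woman treated for one lesion goes on contributing person-time for her other open infections as if her cervix were untouched. If the hazard is lower after treatment, lesion rates are diluted. The hazard ratio for an intervening different-type CIN would then mix any biological effect with tissue removal.

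**Working it through.** **1. The SAP's own figures.** Time = date of event or censoring minus date of onset.
- Subject #4 (9.4.1): 48 − 24 = 24 months, as stated.
- Subjects #1 and #3: 30 − 6 = 24 and 48 − 12 = 36, as stated. Subject #2 in 9.4.2: 48 − 6 = 42, as stated.

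So a different-type CIN3 at Month 42 does not end follow-up. If subject #4 had been excised at Month 42 (an assumption), her time before treatment would be 42 − 24 = 18 months, and 6/24 = 25% of her counted time would lie after treatment.

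**2. Coding of a treated infection.** Take an infection that is positive at one visit, excised before the next and negative at the next. Definition 1 is met. One more negative meets Definition 2. Nothing in 4.3.1, the missing-type rules in 4.5.1, 6.2.6 or 9.3.3 stops the coding as 1.

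**3. Illustration A for clearance (all inputs assumed).** Clearance among untreated infections is u = 55% for HPV-16 and 75% for low-risk types, and 85% are negative after excision. A share t is treated while positive.
- As written: (1 − t)u + 0.85t. Treated excluded: u. Treated not cleared: (1 − t)u.
- At t = 10% and 2%: HPV-16 0.495 + 0.085 = 0.580; low-risk 0.735 + 0.017 = 0.752. Odds ratio (0.580/0.420)/(0.752/0.248) = 0.46. Share of HPV-16 clearances due to treatment: 0.085/0.580 = 15%.

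| Treated, HPV-16 / low-risk | As written | Excluded | Not cleared |
|---|---|---|---|
| 5% / 1% | 0.43 | 0.41 | 0.38 |
| 10% / 2% | 0.46 | 0.41 | 0.35 |
| 15% / 2% | 0.48 | 0.41 | 0.32 |

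**4. Illustration B (other assumed inputs).** Natural clearance is p = 50% for HPV-16 and 65% for the reference. Treated infections all come from those that would not have cleared, and 70% to 90% of them (c) turn negative. Observed clearance = p + tc. The true odds ratio is (0.50/0.50)/(0.65/0.35) = 0.54.
- 5% vs 1% treated: 0.60 to 0.62.
- 10% vs 2%: 0.67 to 0.72.
- 15% vs 3%: 0.75 to 0.83.
- Equal treatment, 10% vs 10%: 0.51 to 0.52.

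The odds ratio moves toward 1 only when HPV-16 is treated more often. Excluding treated infections at 10% vs 2% gives (0.50/0.40)/(0.65/0.33) = 1.25/1.97 = 0.63, so exclusion alone removes only part of this bias.

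**5. Where lesion time is affected.**
- Primary CIN2+: a same-type CIN2+ is the event and ends that infection's time. Time after treatment therefore falls mainly on co-existing infections of other types, which the different-type CIN covariate partly marks.
- CIN3+: a same-type CIN2 is not an event, is not a reason to censor, and is not a different-type lesion. If it is excised, follow-up continues with nothing in the model to mark it.
- If a share f of person-time follows treatment with zero hazard, the observed rate is (1 − f) times the true rate: 0.98, 0.95, 0.90 and 0.80 for f = 2%, 5%, 10% and 20%.

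**The case against.** **Immune clearance is background only.** The objective and endpoint are simply clearance, defined by PCR. That is fair as to wording, but section 1 gives immune clearance as the reason for the analysis, and the determinants are meant to explain it.

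**A rule may sit elsewhere.** Section 4.3 defers to the HPV-008 protocol and the efficacy analysis plan, which are not shown. But it defers the infection categories and histopathological endpoints; clearance and censoring are not named there, and this SAP writes both out in full.

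**The lesion models already adjust.** The different-type CIN covariate separates time after such a lesion, so that time does not simply load onto the HPV-type hazard ratio. This stands for the primary analysis, with the reservation that the covariate records the lesion and not the treatment.

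**Stronger readings that the SAP does not support.**
- A reader might infer that the distortion is worst for HPV-16. No treatment rates by type are given, and in the primary analysis treatment after an HPV-16 CIN2+ adds no HPV-16 time at risk.
- A reader might take subject #4 as a treated woman followed as if untreated. The example does not say that she was treated.
- A reader might take the odds ratios above as estimates of bias. Every input is assumed, and at 5% vs 1% treated in illustration A, exclusion changes 0.43 only to 0.41.

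**Conclusion.** The gap holds on the text for clearance: negativity after excision is coded as clearance, and nothing in the model can adjust for it. The proportion cleared is overstated for treated infections, and comparisons between types are distorted to the extent that treatment rates differ. The size cannot be derived from the SAP. The illustrations run from a shift of 0.02 in the odds ratio to a true 0.54 read as 0.83, depending wholly on the assumed treatment shares and on whether treated infections would have cleared.

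For time to lesion, the primary CIN2+ analysis is exposed in a limited and partly adjusted way. The CIN3+ analyses are exposed more directly. Because the clearest effects concern secondary objectives, this should be fixed, but it is not a defect that invalidates the primary analysis.

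**What to change.** Analysis rules only; no clinical rule is involved.

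- **Treatment date.** Derive each woman's first excisional treatment from the histology records, adding other recorded treatment if available. Section 1 lists no separate treatment record among the data to be used, so completeness should be stated.
- **Sections 4.3.1 and 6.2.6.3.** For infections detected before that date, judge clearance only on samples taken before it. An infection still positive at its last sample before treatment is then not coded as cleared, and Definition 2 needs both negatives before treatment. Report the GEE both with such infections as not cleared and with them excluded, since exclusion alone selects on a consequence of not clearing. In any Cox model of clearance, censor them or treat treatment as a competing event.
- **Sections 6.2.4.4 and 6.2.5.4.** Censor at the treatment date any open infection without a same-type event. Count CIN found in the excision specimen as an event on that date, so that genuine endpoints are not censored. Leave the 12-month time-0 rule unchanged.
- **Reporting.** Give the numbers treated by HPV type, and keep the analysis under the current rules as a sensitivity analysis.

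The cost is SAP wording, one derived date per woman and a few extra model runs. The downside is slightly less person-time and censoring that may be informative, which the paired clearance results and the sensitivity analysis help to expose.

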**Figure 1 Study Overview**

[figure not shown]

- **Experimental design:** A phase III, controlled, multi-center (n=135), and multi-country (n=14) study with two parallel groups.
- **Treatment Groups:** 2 groups: vaccine and control
  - Vaccine: 20µg HPV-16 L1 VLP/20µg and HPV-18 L1 VLP/50µg MPL®/ 500µg aluminum in the form of Al(OH)3,
  - Control: Hepatitis A vaccine (Havrix™-based investigational formulation) (720 ELISA units of antigen; 500µg aluminum in the form of Al(OH)3).
- **Treatment allocation:** Randomized (1:1).

- **Randomization method:** SBIR (Internet randomization).
- **Blinding:** Double-blind.
- **Enrolment period:** May 2004 to June 2005.
- **Study regions:** Asia Pacific, Europe, Latin America and North America.
- **Enrolled:** 18729 subjects aged 15-25 years. Total Vaccinated Cohort (TVC): 18644 subjects. Total Vaccinated Cohort for efficacy 1 (TVC-1): 18525 subjects.
- **Control arm** (HAV vaccine group): TVC: 9325 subjects. TVC-1: 9267 subjects.
- **Vaccination schedule(s):** Three doses of HPV vaccine or HAV vaccine (control arm) administered on a Month 0, 1, 6 schedule.
- **Study visits:** 10 study visits per subject scheduled at Months 0, 1, 6, 7, 12, 18, 24, 30, 36 and 48.
- **Total duration of the study:** 48 months of follow-up from study entry planned for all subjects.
- **Database freeze for the final analysis:** October 2008; **Database freeze for the M48 analysis:** March 2010.

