#### 4.3.1 Cervical HPV infections

- **Incident cervical HPV infection:** an incident cervical infection with a given HPV type is defined as the new detection of this HPV type (by PCR) at any time point during the follow-up period (i.e. after enrolment in the control arm of study HPV-008).
- **Transient cervical HPV infection:** a transient cervical infection with a given HPV type is defined as the detection of this HPV type (by PCR) at any single time point during the follow-up period followed by a negative sample for that HPV type at the evaluation performed 6 months after the evaluation when the cervical HPV infection was first detected.
- **6-month persistent cervical HPV infection:** a persistent cervical HPV infection (6-month definition) is defined as the detection of the same HPV type (by PCR) in cervical samples at two consecutive evaluations over approximately a 6-month interval. Thus, the algorithmic definition of a 6-month persistent infection is that there exists a sequence of positive samples with the same HPV type, not interrupted by negative samples, such that the total range is more than 5 months ( $> 150$  days). The start of the persistent cervical HPV infection is defined as the date of the first positive sample in the sequence.
- **12-month persistent cervical HPV infection:** a persistent cervical HPV infection (12-month definition) is defined as the detection of the same HPV type (by PCR) at all available time points over approximately a 12-month interval. Thus, the algorithmic definition of a 12-month persistent cervical infection is that there exists a sequence of positive samples with the same HPV type, not interrupted by negative samples, such that the total range is more than 10 months ( $> 300$  days). The start of the persistent cervical HPV infection is defined as the date of the first positive sample in the sequence.
- **Other cervical HPV infection:** other cervical HPV infections than those described above will be considered in the analysis. These infections are cervical HPV infections with duration less than 150 days and cervical HPV infections detected at the last visit and for which it is not possible to determine if they are transient or persistent.

- **Clearance of cervical HPV infection:** two definitions will be used:

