### 4.5 Handling of missing data and inconsistencies

#### 4.5.1 Missing HPV type at visits

The following rules will be applied for the determination of cervical HPV infections in case HPV type is missing at visits:

| Visit v  | Visit v+1                     | Visit v+2                     | Rule for the determination of cervical HPV infections and clearance                                                                                                          |
|----------|-------------------------------|-------------------------------|------------------------------------------------------------------------------------------------------------------------------------------------------------------------------|
| HPV-X    | Missing HPV type              | HPV-X                         | If the duration between detection date of HPV-x at visit v and detection of HPV-x at visit v+2 is > 150 days → 6-month persistent cervical HPV infection starting at Visit v |
| HPV-X    | Missing HPV type              | No HPV-X                      | Transient cervical HPV infection at Visit v
Clearance* (according to definition 1) of cervical HPV infection at visit v+2                                                 |
| HPV-X    | Missing HPV type (last visit) | -                             | No clearance of HPV-X at visit v+1                                                                                                                                           |
| No HPV-X | HPV-X                         | Missing HPV type (last visit) | Other cervical HPV infection at Visit v+1
No clearance of HPV-X at visit v+2                                                                                              |

\*Clearance (according to definition 2) if there is no HPV of type x at visit v+3.

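### Transient status and Definition 1 clearance depend on a PCR 6 months after the positive sample, which the schedule lacks after Month 36; the SAP leaves the Month 36 to 48 interval unresolved

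*SAP*

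**What the plan says.** **Schedule.** SAP 3.2 states that "HPV DNA typing by PCR was performed on cervical liquid-based cytology samples at Months 0, 6, 12, 18, 24, 30, 36 and 48". The design summary under Figure 1 agrees: "10 study visits per subject scheduled at Months 0, 1, 6, 7, 12, 18, 24, 30, 36 and 48". Nothing is scheduled between Months 36 and 48.

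**Transient infection (4.3.1).** A detection at a single time point must be "followed by a negative sample for that HPV type at the evaluation performed 6 months after the evaluation" of first detection.

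**Clearance, Definition 1 (4.3.1).** At least one negative sample is needed "at the evaluation performed 6 months after the evaluation when the incident or transient cervical HPV infection was detected", or 6 months after the last positive sample of a persistent infection. Definition 2 asks for two negatives.

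**Persistence (4.3.1).** This wording is looser, "at two consecutive evaluations over approximately a 6-month interval", and is backed by an algorithm: an uninterrupted run of positives spanning more than 150 days, or more than 300 days for the 12-month version.

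**Missing results (4.5.1).** For the sequence positive, missing HPV type, negative, the table assigns a transient infection at visit v and "Clearance* (according to definition 1) of cervical HPV infection at visit v+2". Its footnote grants Definition 2 only if visit v+3 is also negative.

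**Coding (6.2.6.3).** Clearance is binary, 0 or 1, with no level for infections that cannot be assessed.

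**The concern.** The 6-month rule fits every PCR interval except the last, which is 12 months. Take an infection last positive at Month 36 with a negative sample at Month 48. The negative was observed, but not at an evaluation 6 months after the positive one. A programmer who follows 4.3.1 to the letter would code no clearance. A programmer who follows the logic of 4.5.1 would code clearance.

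Under the literal reading the outcome becomes partly a function of visit month, and the proportion cleared is understated for late infections. In the GEE models of 6.2.6.4, a determinant associated with late detection could then pick up an odds ratio produced by the schedule.

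In the any-infection analysis, the transient label feeds the infection-category covariate (Annex 9.5.1) and the ranking that links a lesion to one of several same-type infections (6.2.5.3).

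**Working it through.** **Step 1: which last-positive visits have the required PCR.** Grid from SAP 3.2: 0, 6, 12, 18, 24, 30, 36, 48. The gaps are six of 6 months, then one of 12.

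| Last positive | PCR 6 months later? | Any later PCR? | Two later PCRs (Definition 2)? |
|---|---|---|---|
| Months 0 to 30 | yes | yes | yes |
| Month 36 | no | yes (Month 48) | no |
| Month 48 | no | no | no |

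Month 36 is the only visit at which a later sample exists but the worded rule cannot use it.

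**Step 2: the same interval under the other rules.** Positive at both Months 36 and 48 spans about 12 × 30.44 = 365 days, so it passes both the 150-day and the 300-day persistence limits. Positive then negative over the same interval fails the literal transient and clearance wording. Under 4.5.1, positive, missing, negative on a 6-month grid also spans 12 months and is transient and cleared. The same information is therefore classed differently according to whether a result was missing or no visit was scheduled.

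**Step 3: does the SAP say how to number Month 48?** It does not say whether Month 48 is v+1 or v+2 after Month 36. The Annex 9.4 grids add to the doubt: they have a Month 42 column and no Month 18 column, and subject #5 in 9.4.3 has a transient HPV18 infection detected at Month 42, where SAP 3.2 lists no PCR.

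**Step 4: possible size.** The SAP gives no counts, so these inputs are assumed: constant onset rate, exponential duration with median m of 6, 12 or 18 months, perfect PCR, full attendance. Let q = 2^(−6/m), the chance that an infection lasts another 6 months.

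The number with last positive at visit v is proportional to P(v) × (1 − chance of lasting to the next PCR). If onset is confined to Months 0 to 48, P(v) = 1 − q^(v/6). If the same onset rate held long before enrolment, P(v) = 1 at every visit. Infections still positive at Month 48 count as not cleared under either rule.

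Worked case, m = 6 (q = 0.5), onset within Months 0 to 48:
- last positive at Months 6 to 30: 0.250 + 0.375 + 0.4375 + 0.46875 + 0.484375 = 2.0156
- last positive at Month 36: 0.984375 × (1 − 0.25) = 0.7383
- positive at Month 48: 1 − 0.5^8 = 0.9961
- total = 3.750
- cleared at next PCR: (2.0156 + 0.7383)/3.750 = 73.4%
- cleared, literal rule: 2.0156/3.750 = 53.8%

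| Onset | m (months) | Next PCR | Literal | Drop (points) | Month 36 share of next-PCR clearances |
|---|---|---|---|---|---|
| Months 0 to 48 only | 6 | 73% | 54% | 20 | 27% |
| | 12 | 58% | 39% | 19 | 33% |
| | 18 | 48% | 30% | 17 | 36% |
| Also before Month 0 | 6 | 79% | 63% | 16 | 20% |
| | 12 | 69% | 54% | 15 | 22% |
| | 18 | 62% | 47% | 14 | 23% |

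Drops are taken from unrounded values. A simulation under the same assumptions agrees.

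**The case against.** **The plan read as a whole may allow the sensible coding.** If Month 42 is treated as a visit without a result, 4.5.1 makes a Month 36 positive with a Month 48 negative transient and cleared. If Month 48 is v+1, it is simply the next evaluation. The sequences tabulated as no clearance (4.5.1 and Annex 9.2) all lack a PCR result after the last positive. This stands. A reader might infer from 4.3.1 that infections last positive at Month 36 can never clear or be transient; the documents do not support that for Definition 1 or for transient status. But 4.5.1 is written for a missing HPV type at a visit, and Month 42 is not a scheduled visit, so the interval stays open.

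**Coding as 0 is an inference.** Section 6.2.6.3 lists only the two codes. Section 4.3 also refers to the HPV-008 protocol and the efficacy analysis plan, and the flowchart in Annex 9.2 is not shown; any of these might settle the point. That is fair, and it limits the claim to the text at hand.

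**Transient is the natural remaining category.** Of the four levels in 4.4.2, a single Month 36 positive is neither 6-month persistent nor detected at the last visit. However, 4.3.1 also has a group for infections lasting less than 150 days, which 6.2.5.3 ranks above transient, so the level is not settled by elimination.

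**The size is assumption-driven.** This stands. Whether infections already present at Month 0 enter the clearance analysis is itself unclear: 6.2.6.3 speaks of incident infections, while Annex 9.3.3 says all are included. That is why both settings are shown.

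**The primary analysis is untouched.** This stands. It runs from 6-month persistent infection to CIN2+ and does not use the transient category. A clearance first seen at Month 48 cannot separate two persistent infections, because no later scheduled sample follows.

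**Conclusion.** The point holds as an unresolved conflict in the SAP. The 6-month wording of 4.3.1 has no matching PCR after Month 36. Followed literally, it fails to recognise an observed negative at Month 48, against 4.5.1 and out of step with the persistence rule over the same interval.

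If the literal reading were coded, the proportion cleared would fall by about 14 to 20 percentage points. This rests on constant onset, exponential duration with median 6 to 18 months, perfect PCR and full attendance. The true figure cannot be computed from the SAP, and the loss is nil if the next-PCR reading is used.

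One strict impossibility does exist, in Definition 2: only one scheduled PCR follows Month 36, so two later negatives cannot be observed under any reading.

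The consequences lie in the secondary clearance analysis and in the infection category and lesion linkage of the any-infection models.

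**What to change.** - **4.3.1:** judge transient status and Definition 1 clearance at the next available PCR after the positive sample (for clearance, after the last positive). This agrees with 4.5.1 and removes the question of how Month 48 is numbered.
- **Long gaps:** flag infections whose first negative comes more than about 9 months after the last positive, so that they can be shown separately.
- **Definition 2:** state that two later negatives cannot be observed when the last positive is at Month 36, and treat those infections as not assessable instead of coding them 0.
- **Annex 9.4:** reconcile the columns (Month 42 present, Month 18 absent) and the Month 42 HPV18 example with the schedule in 3.2.

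The cost is a wording change, about one line of derivation code for the main rule, a flag and a not-assessable level for Definition 2. The small downside is that transient will include infections whose negative came about 12 months later, which 4.5.1 already accepts.
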